##### School performance

Parents will complete the eight-item Concussion Learning Assessement and School Survey to measure post-injury academic experiences, including number of days missed, concerns about school performance, impact on grades, and whether the school provides academic support to kids with concussion [74]. This will be repeated at each of the follow-up assessments. Participants’ 1 year pre- and post-injury school attendance and grades will also be obtained from school records as a measure of academic outcomes [31] and will be re-coded using a standardized four point grade-point average (GPA).

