Baseline injury, demographic, or clinical variables found to be statistically significant in this analysis will also be included as covariates in the regression models. Some attrition is expected in the study samples. In prior randomized trials of injured adolescents, the investigative group has achieved 6–12-month follow-up completion rates ≥ 90% [31]. Estimates derived from these rates are incorporated into descriptions of subject flow and power analyses. Assumptions about the nature of missing data are crucial to the type of statistical analysis chosen [87–89]. Full information maximum likelihood estimates from mixed random effects generalized linear models adjust for data missing at random (MAR) [90].

We will use statistical logistic models to determine which, if any, demographic or clinical characteristics, including treatment group membership, are predictive of subject attrition. Any factors observed to explain trends in missing data would be used as covariates in subsequent analyses. In past studies, no sources of consistent variation to explain missing data were found. Based on our low attrition rates and the lack of consistent variation in past investigations, we believe that MAR is a reasonable assumption. However, we will perform a sensitivity analysis using non-MAR techniques. The analysis of missing data is an area of ongoing development, and the investigative group will incorporate the most contemporary approaches in the final analyses [88, 89].

We will test for changes in the GPA at 12 months compared to pre-injury in the intervention group participants compared to those in the control group. We will also examine differences in the scores on standardized tests in the same fashion, as well as examine for differences in time lost from school, including missing whole days as well as missing partial days. Secondary analyses will explore the associations with gender, type of sports injury, pre-injury history of psychiatric disorder or visits, and cumulative lifetime trauma history and any observed treatment effects.

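### GPA is to be compared as change from pre-injury, which is valid but less precise than adjusting 12-month GPA for the pre-injury GPA already planned for collection

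*Protocol article*

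**What the plan says.** Improving school performance is the third of four aims under *Objectives and hypothesis*, and *School performance* is listed among the secondary outcome measures. That section plans the pre-injury data: "1 year pre- and post-injury school attendance and grades will also be obtained from school records as a measure of academic outcomes". Grades are to be recoded to a four-point GPA, and Table 1 lists school records at baseline and 12 months.

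The analysis is set out in *Data analysis plan and statistical procedures*:

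- GPA: "We will test for changes in the GPA at 12 months compared to pre-injury in the intervention group participants", with the usual-care arm as comparator.
- Standardized tests: "We will also examine differences in the scores on standardized tests in the same fashion".
- Time lost: the team will "examine for differences in time lost from school, including missing whole days as well as missing partial days".

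No pre-injury school value is named as a covariate for any of these. The mixed models in the same section are introduced for symptom and quality-of-life outcomes, and school outcomes are not on that list. The covariate rule reads: "Baseline injury, demographic, or clinical variables found to be statistically significant in this analysis will also be included as covariates in the regression models". The analysis it refers to is a test of baseline differences between arms. School variables are not named in it.

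**The concern.** A change score fixes the coefficient on pre-injury GPA at 1. Regression adjustment estimates that coefficient from the data. When the pre/post correlation is below 1, the fixed coefficient over-corrects and the treatment comparison carries more variance than it needs to. The arm that happens to start higher will also tend to show the larger fall.

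The rest of the section does not clearly repair this. The mixed models are tied to other outcomes. The covariate rule admits variables only when the arms differ significantly, so a strongly prognostic but balanced pre-injury GPA would stay out and its precision would be lost.

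At stake is power for one of the four aims. The article gives no power calculation for any school outcome, so there is no known reserve to absorb the loss.

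**Working it through.** **Inputs from the article (*Power analysis and sample size*).** 180 participants retained, taken as 90 per arm; two-sided alpha 0.05; ρ = 0.7 between assessments. The ρ was chosen for the powered symptom and quality-of-life outcomes, not for GPA.

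**Assumptions.** A GPA correlation of 0.5 to 0.9, equal GPA SD before and after, and an illustrative GPA effect of d = 0.30 SD. The article gives none of these.

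**The article's own figures first.** None exists for a school outcome. The nearest are 0.80 power at d = 0.36 (HBI) and at d = 0.37 (PedsQL). Take power = Φ(d/√(2v/90) − 1.96), where v is the variance factor in units of SD². With the four-visit average, v = (1 + 3 × 0.7)/4 = 0.775 and √(2 × 0.775/90) = 0.131. The results are 0.783 at d = 0.36 and 0.805 at d = 0.37. Both lie within 2 points of the stated value, so the formula suits the comparison below.

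**Variance of the two GPA analyses.**

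- Change score: v = 2(1−ρ)
- Adjusted for pre-injury GPA: v = 1−ρ²
- Ratio, change to adjusted: 2/(1+ρ)

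| Assumed ρ | v, change | v, adjusted | Ratio | Power, change (d = 0.30) | Power, adjusted (d = 0.30) |
|---|---|---|---|---|---|
| 0.5 | 1.00 | 0.75 | 1.33 | 0.521 | 0.642 |
| 0.7 | 0.60 | 0.51 | 1.18 | 0.738 | 0.805 |
| 0.9 | 0.20 | 0.19 | 1.05 | 0.994 | 0.996 |

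Worked at ρ = 0.7: the change score has standard error √(2 × 0.60/90) = 0.115 SD, giving Φ(0.30/0.115 − 1.96) = 0.738. Adjustment has √(2 × 0.51/90) = 0.106 SD, giving 0.805. The ratio is also the sample-size ratio, so the change score needs about 33%, 18% and 5% more participants for equal power.

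**Is the change score biased?** In 20,000 simulated trials per correlation (90 per arm, no treatment effect), its mean error was −0.0017, 0.0003 and −0.00001 SD at ρ = 0.5, 0.7 and 0.9. Its rejection rate was 4.99%, 5.08% and 4.90%. It is therefore unbiased over randomizations and holds its 5% level.

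**What remains given an observed imbalance.** If the arms differ by D at pre-injury, the change score has conditional error −(1−ρ)D. The simulated slopes on D were −0.493, −0.294 and −0.099, against −0.5, −0.3 and −0.1 in theory. One standard error of D with 90 per arm is √(2/90) = 0.149 SD. An imbalance of that size gives an error of about −0.075, −0.045 and −0.015 SD at ρ = 0.5, 0.7 and 0.9.

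**The case against.** **A reader might infer that chance pre-injury differences bias the result.** They do not. Under 1:1 randomization the change-score comparison is unbiased and its type I error is right. The error given an observed imbalance is the same imprecision seen from another side, not a second harm. The ceiling of the four-point scale does not support a bias claim either, since a linear regression on pre-injury GPA meets the same ceiling.

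**The model may be settled elsewhere.** The article names a contrast, not an estimator, and excludes no covariate. It also states a general intent to control for known confounders. A full protocol or analysis plan, not shown, could adjust. This stands in part: that the change would be left unadjusted is a natural reading, not a stated fact. But the article does commit to a change contrast for GPA, and a plan that followed the sentence would inherit the lower precision.

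**The size is borrowed.** This stands. The ρ of 0.7 was not chosen for yearly grades, and d = 0.30 is illustrative. If GPA is highly stable the gain is very small.

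**Time lost from school.** A reader might infer that pre-injury attendance will go unused and that power is heavily reduced. The article is silent on the model, and it collects pre-injury attendance as an academic measure, which points to some use. The factor 1−ρ² is a linear-model result and does not carry over directly to a count model. The article gives no correlation between absence before and after injury. It also does not say that school records capture partial days. No size can be given for this outcome.

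**Pre-injury records for every participant.** This is an intention that depends on release and retrieval of school records. The article gives no completeness figure.

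**Conclusion.** The point holds as a matter of efficiency. The stated GPA comparison is valid, unbiased over randomizations and correctly sized, but a more precise analysis is available from data already planned. The cost of the change score is about 33% more participants at ρ = 0.5, 18% at 0.7 and 5% at 0.9. At an assumed d of 0.30 with 90 per arm and ρ = 0.7, power is 74% against 80%.

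These figures assume equal variances before and after and a linear model, and they ignore the one degree of freedom spent on the covariate. The result is sensitive to the GPA correlation, which the article does not give.

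No power or sample-size figure in the article is shown to be wrong, and the outcome is secondary. This is an improvement to make at almost no cost, not the correction of an invalid test.

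**What to change.** In *Data analysis plan and statistical procedures*:

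1. Replace the GPA change test with a regression of 12-month GPA on treatment arm and pre-injury GPA. Include pre-injury GPA regardless of any baseline significance test. Report the adjusted between-arm difference with its confidence interval.
2. Treat standardized tests the same way where a pre-injury score exists. The *School performance* section mentions attendance and grades from school records but not test scores, so availability should be confirmed.
3. For time lost from school, name pre-injury attendance from school records as a covariate where it is available, in a model suited to the outcome.

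The cost is a few sentences of analysis wording, with no further participants. For GPA no data are needed beyond the school records already planned. The usable sample for each outcome depends on how completely those records are retrieved.

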### Objectives and hypothesis

This study was designed to assess whether adolescents with persistent symptoms after sports-related concussion will demonstrate better outcomes when receiving a collaborative care intervention compared to usual care (control) condition. Four main aims are addressed; first, we want to compare the groups with respect to post-concussive, anxiety, and depressive symptoms at 3, 6, and 12 months follow-up. Second, we seek to examine the effectiveness of the intervention in improving function and health-related quality of life among adolescents with persistent symptoms after sports-related concussion. Third, the study will also evaluate the impact of the collaborative care intervention on school performance. Finally, we aim to explore the heterogeneity of treatment effects in outcomes by examining the interaction of the treatment effect with group membership in distinct subgroups of the population.

We hypothesize that adolescents who receive the collaborative care intervention will demonstrate clinically and statistically significant reductions in PCS and depressive and anxiety symptoms over the course of the 12-month study compared to the usual care control group. We also hypothesize that adolescents who receive collaborative care will exhibit a clinically meaningful improvement in functioning and health-related quality life compared to the usual care control group. For the third aim, we expect that adolescents who receive the collaborative care intervention will receive individualized treatment and community resource linkages which will improve their school performance and return to full activities at school compared to usual care. Finally, we anticipate that three distinct subgroups will emerge from the study population—adolescents who recover from symptoms, adolescents with chronic psychosocial problems, and adolescents whose symptoms wax and wane over time—and these groups will have heterogeneity in treatment effects.

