##### Exposure to life stress

For adolescent subjects we will use the UCLA Reaction Index Trauma History to collect information at baseline [80]. This measure asks whether or not the respondent has ever experienced ten specific and different traumatic events. The Life Events Checklist will be collected at the 6- and 12-month time points, asking the respondent about whether or not specific life events occurred in the past 6 months, if the event was good or bad, and the level of effect the event had on the respondent’s life. For parent participants we will use an adapted version of the questionnaire used in the National Comorbidity Study–Trauma History at baseline [81]. This will ask about prior abuse, assault, witnessing or experiencing an accident, disaster, life threating illness, death of loved ones. At 6- and 12-month time points we will use the Stressful Life Events Scale, which asks whether or not a parent has experienced specific events [82].

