We will examine heterogeneity of treatment effects in the primary and secondary outcomes by examining the interaction of the treatment effect with group membership in distinct subgroups of the population. These will be exploratory analyses. Based on our clinical experience, we hypothesize at least three groups of patients: (1) children with mild PCS who, while the symptoms last longer than for most children, nevertheless do resolve relatively quickly; (2) a group of children with persistent PCS and prior history of substantial psycho-emotional distress; (3) a group of children who have symptoms that affect their quality of life, but which wax and wane over time. We will explore defining these groups (1) a priori using clinical indicators and symptoms and (2) empirically using the study sample data, such as latent profile analysis or trajectory analysis. The analysis will define these groups and examine the heterogeneous effect of the intervention of the recovery profiles of these groups.

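### The exploratory heterogeneity aim allows subgroups to be formed from follow-up trajectories, which treatment itself changes; subgroups used as effect modifiers should come from baseline data only

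*Protocol article*

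**What the plan says.** The protocol article, under Data analysis plan and statistical procedures, sets out the heterogeneity analysis for the primary and secondary outcomes as "examining the interaction of the treatment effect with group membership in distinct subgroups of the population". It gives two ways to form the groups: "a priori using clinical indicators and symptoms", and "empirically using the study sample data, such as latent profile analysis or trajectory analysis". It labels the work: "These will be exploratory analyses".

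Three groups are expected. The first is "children with mild PCS who, while the symptoms last longer than for most children, nevertheless do resolve relatively quickly". The second combines persistent symptoms with a history of psychological distress. The third is "a group of children who have symptoms that affect their quality of life, but which wax and wane over time". Under Objectives and hypothesis the same groups are named as "adolescents who recover from symptoms, adolescents with chronic psychosocial problems, and adolescents whose symptoms wax and wane over time".

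Neither section says that the grouping uses only information available before randomization.

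**The concern.** A treatment-by-subgroup interaction has its usual meaning when treatment cannot change subgroup membership. Recovering, or waxing and waning, over the trial year is a course observed after randomization. It is also the outcome: the main analysis compares longitudinal symptom trends between the arms.

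If collaborative care works, it moves some patients from a worse course to a better one. Part of the benefit then appears as a difference between arms in class membership. Within a class, intervention and control patients have been selected to have similar courses, so their difference is smaller than the true effect and no longer rests on randomization. At stake is what the trial says about who benefits, which is one of its four stated aims.

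**Working it through.** **Inputs from the protocol** (Power analysis and sample size; Design): 1:1 allocation with 180 retained, so 90 per arm; visits at baseline, 3, 6 and 12 months; equal correlation 0.7; HBI baseline mean 33.0 and SD 11.0; d = 0.36, which is 0.36 × 11 = 3.96 HBI points; pilot d = 0.74, which is 0.74 × 11 = 8.14 points.

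**Assumptions, not in the protocol**: control mean HBI of 33, 28, 25 and 22 at the four visits; three classes (four in a sensitivity run); classes found by k-means or a Gaussian latent profile model on all visits, or by k-means on changes from baseline.

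**1. The plan's own power figure.** The protocol gives no figure for the subgroup analysis, so only the main one can be reproduced. For an omnibus group-by-time F test the noncentrality is 2n × Σ(m − mean m)² / (1 − ρ), where m is half the arm difference at each visit in SD units. For a difference growing linearly with calendar time (0, 0.09, 0.18, 0.36), m = 0, 0.045, 0.09, 0.18 and Σ = 0.0177, so the noncentrality is 180 × 0.0177 / 0.3 = 10.6 and power is 0.786. With equal steps (0, 0.12, 0.24, 0.36) it is 180 × 0.018 / 0.3 = 10.8 and power is 0.793. Both agree with the stated 0.80, so the inputs are a fair basis.

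**2. The same true effect for every patient.** The effect is present at all three follow-ups. The 12-month HBI is regressed on group indicators, treatment and baseline HBI; the treatment coefficient is the average within-group effect.

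| How groups are formed | Within-group effect, true −3.96 | Share lost | Power | Within-group effect, true −8.14 |
|---|---|---|---|---|
| Baseline HBI | −3.98 | none | 0.91 | −8.09 |
| Trajectory, all visits | −2.0 to −2.1 | about half | about 0.5 | about −4.1 |
| Trajectory, change scores | −1.0 | 1 − 1.0/3.96 = 75% | about 0.2 | about −2.0 |

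The mechanism is visible in the change-score grouping at d = 0.36: 38% of the intervention arm but 19% of controls fall into the best class. With no treatment effect, 29% of each arm do, and the within-group estimate is unbiased.

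**3. Sensitivity.** Over correlations of 0.5 to 0.8, three or four classes, and an immediate or gradual effect, the true −3.96 becomes −3.08 to −0.82. The loss is therefore 1 − 3.08/3.96 = 22% to 1 − 0.82/3.96 = 79%. The smallest losses occur with a gradual effect and high correlation.

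**4. The planned test, the interaction.**
- Uniform effect, one population: rejection stays near 5% with either kind of grouping.
- Uniform effect, three genuine pre-existing classes (assumed class means; within-class SD 5 or 8; correlation 0.5): with the true classes the effect is about −3.95 and false interaction about 4%. With classes estimated from trajectories the effect is −2.3 (SD 5) or −1.4 (SD 8), and false interaction is 14% or 9%.
- Real heterogeneity by a baseline factor that splits patients in half, effect 0 in one half and 2d in the other: at d = 0.36, interaction power is 0.92 with that factor and 0.08 to 0.09 with trajectory groups; at d = 0.74 it is 1.00 against 0.21 to 0.31. Testing the correct factor is a best case, so this gap is an upper limit.

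**The case against.** **The plan does not commit to trajectory groups.** The a priori clinical route stands beside the empirical one, trajectory analysis is an example, and latent profile analysis, named first, would be sound if fitted to baseline variables. This stands: a reader might infer that the whole aim rests on outcome-defined groups, and the protocol does not say that. But trajectory analysis needs repeated measurements, and neither route is restricted to baseline.

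**The group descriptions are partly baseline.** Mild symptoms and prior distress can be recorded at entry, and because entry is 1 to 9 months after injury, some course precedes randomization. This is fair for the second group and part of the first. Quick resolution, and waxing and waning, would still be judged largely on follow-up.

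**The analysis is exploratory.** True, and it limits the consequence. The label guards against overclaiming; it does not remove bias from the comparison.

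**The details belong in the analysis plan, which is not shown.** A latent-class model that treats class as fixed before randomization, with class-specific treatment effects, could avoid much of the problem. The article specifies no such model. The point concerns a method that the article names, not a missing detail.

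**Life events as moderators.** Under a heading on moderators the protocol states: "The Life Events Checklist will be collected at the 6- and 12-month time points". A reader might infer that these post-randomization events will be tested as effect modifiers. The documents do not say so. The factors listed for secondary analyses are gender, injury type, pre-injury psychiatric history and cumulative lifetime trauma, and trauma history has a baseline instrument. This is not counted as an error.

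**Conclusion.** The concern holds for one named route within an exploratory aim. If groups are formed from follow-up trajectories and then used as effect modifiers, within-group effects are attenuated whenever treatment works. Under the plan's SD, correlation, sample size and d = 0.36, roughly 20% to 80% of a uniform effect is lost, and true heterogeneity by a baseline factor can be missed. The size rests on the assumed mean trajectories, number of classes and clustering methods, so the range matters more than any single figure.

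Two stronger readings are not supported. A reader might infer that the benefit would disappear in every class; that occurs only if treatment acts solely by moving patients between classes, and in the simulations part of the effect remained. A reader might also infer that the trial's main conclusion is at risk; the primary intent-to-treat comparison does not use these groups. It is a correction worth making, not a threat to the trial.

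**What to change.** State that any subgroup used as an effect modifier is defined only from variables measured before randomization: for example baseline HBI, time since injury, baseline PHQ-9 and GAD-7, prior psychiatric history and baseline trauma history. The groups may be set by clinical rule or by latent profile analysis of those baseline variables.

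If trajectory classes are of interest, compare class proportions between the arms as an outcome, or predict class from baseline variables and use the predicted class as the modifier.

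The cost is a change of wording; the baseline measures are already collected. The downside is that baseline-defined classes may separate less clearly than trajectory classes.

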#### Power analysis and sample size

Power analyses were conducted using PASS software to determine the appropriate number of participants for the study [91–93]. Based in part on prior investigation by the study team, assumptions including four assessment points (baseline, 3 months, 6 months, and 12 months), equal correlations over time of ρ = 0.7, two-tailed alpha = 0.05, and 10% 12-month attrition were used for all power analyses. We used data derived from our prior large scale collaborative care investigations to estimate symptomatic and quality of life treatment effects for power calculations [25, 94]; data from the pilot were used to corroborate treatment effect estimates derived from these larger scale trials [95, 96]. The study team conservatively estimated that the 12-month persistent concussive symptom treatment effect will be d = 0.35–0.40, using preliminary data derived from prior study team large scale collaborative care investigations [25, 31].

To estimate the power to detect a group-by-time interaction effect on persistent concussive symptoms we used the primary continuous HBI total symptom score with baseline mean = 33.0 and common SD = 11.0. The study will require recruitment of 200 subjects (100 subjects in each group) in order to retain 180 subjects at the 12-month post-injury follow-up. With a final sample of 180 subjects, the power to detect a significant group-by-time interaction with a between-group effect size of d = 0.36 on the HBI somatic symptom scale is 0.80.

The study team also estimated the power to detect between-group differences in 12-month treatment response rates based on a response cutoff level of three or more symptoms on the HBI. If at the 12-month study endpoint 44% of subjects in the intervention group vs 65% of subjects in the control group continue to meet the PCS symptomatic criterion of three or more symptoms on the HBI, the power is = 0.80. Data from the collaborative care pilot corroborate these estimates. The pilot demonstrated a 0.74 treatment effect on the 6-month symptoms measured by the HBI [36]; with 180 subjects the power to detect a significant treatment group difference is ≥ 90%. In our prior R01 study, the 12-month post-injury treatment effects for the Medical Outcomes Study Short Form 12/36 Physical Components Summary were approximately 0.30 [25]. In the current study we use a PEDS-QL study entry baseline of 59.0 and common SD of 14.4. Anticipating an effect size of d = 0.37 with 90 subjects in each group, the power to detect a significant group by time interaction effect is 0.80. The pilot study demonstrated a 0.66 treatment effect on the HBI; with 180 subjects the power to detect a significant treatment group difference is ≥ 90%.

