### Outcome evaluation

For all adolescents enrolled in the trial, follow-up surveys will be completed online or by telephone at 3, 6, and 12 months after the traumatic injury, with monetary incentives for each. Participants will be invited to complete follow-up surveys even if they have discontinued or not fully engaged in the intervention protocols. Research assistants will be trained to bring up specific discussion points about the benefits of study participation in cases where control group families are unsure about continuing their participation, to increase their retention and counteract differential dropout. Table 1 provides a summary of data collection time points. The study includes a variety of outcome measures to cover the wide gamut of issues experienced by youth with persistent post-concussive symptoms, such as depression, anxiety, sleep interference, headaches, and poor school performance.

**Table 1 Tab1:** List of study measures by timepoint

Construct	Measure	Screen	Base-line	3 months	6 months	12 months
History of TBI		P	P			P
Post-concussive symptoms	HBI	A, P	A, P	A, P	A, P	A, P
Depressive symptoms	PHQ-9		A, P, PS	A, P, PS	A, P, PS	A, P, PS
Anxiety symptoms	Generalized Anxiety Disorder-7 item, revised Child Anxiety and Depression Scale		A, PS	A, PS	A, PS	A, PS
Quality of life	Peds Quality of Life		A, P	A, P	A, P	A, P
Exposure to life stress–adolescent	UCLA Reaction Index Trauma History, at baseline; Life Events Checklist–Child Form at 6 and 12 months		A		A	A
Exposure to life stress–parent	National Comorbidity Study –Trauma History measure at baseline; LES at 6 and 12 months		PS		PS	PS
Sleep	Adolescent Sleep-Wake Scale		A	A	A	A
Headache	TBI-QL–Headache Pain		A	A	A	A
School attendance and performance	Questionnaire and school records		P, SR	P	P	P, SR
Satisfaction with care	Client Satisfaction Questionnaire				A, PS	
Prior psychiatric history	Questionnaire		P			
Demographic characteristics	Questionnaire		PS			
Health Service and Medication Utilization	Questionnaire		P	P	P	P

*A* adolescent, *P* parent report of youth, *PS* parent self-report, *SR* school records, *TBI* traumatic brain injury

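### The HBI is scheduled twice before randomization, but the screening score has no stated role in the HBI models; entering it as a pre-specified covariate would give a small gain of uncertain size

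*Protocol article*

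**What the plan says.** The protocol article's Table 1, titled "List of study measures by timepoint", has five columns: screening, baseline, 3, 6 and 12 months. The HBI row is filled for adolescent and parent in all five: "HBI A, P A, P A, P A, P A, P". Under Masking of treatment allocation, the envelopes are opened after the baseline assessments. Each reporter therefore has two scheduled HBI readings before randomization.

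The section Power analysis and sample size works with "four assessment points (baseline, 3 months, 6 months, and 12 months", together with "equal correlations over time of ρ = 0.7", "two-tailed alpha = 0.05" and "10% 12-month attrition were used for all power analyses". The HBI inputs are "baseline mean = 33.0 and common SD = 11.0", with "recruitment of 200 subjects (100 subjects in each group) in order to retain 180 subjects". Stated power is 0.80 for a group-by-time interaction at d = 0.36.

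The section Data analysis plan and statistical procedures specifies mixed models with a time-by-treatment interaction. It does not list the assessments that enter the model, and it neither mentions nor excludes the screening HBI. It gives two routes by which a pre-randomization variable becomes a covariate: a significant difference between arms at baseline, or an observed association with attrition.

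**The concern.** The screening HBI is a second reading of the main symptom score. Treatment cannot have affected it, and it is already on the schedule. Two readings usually predict follow-up better than one, because each carries its own measurement error and day-to-day variation.

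Neither stated covariate route asks whether a variable predicts the outcome. A strongly prognostic screening score would stay out of the model if the arms happened to be balanced on it and it did not predict dropout. A significance test between randomized arms detects only chance imbalance, so it is a poor way to choose covariates.

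At stake is some precision on the HBI comparison, for which the plan allows power of 0.80 and no reserve. Validity is not at stake.

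**Working it through.** **Inputs.** From the power section: 90 per arm analysed, correlation 0.7 between all pairs of baseline, 3, 6 and 12 months, two-sided alpha 0.05, difference 0.36 SD at 12 months, SD 11.0. Not in the article, so assumed: the full HBI is scored at screening; its correlation with baseline (*a*) is 0.5 to 0.95; its correlation with follow-up (*b*) is 0.5 to 0.7.

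**The plan's own figure.** For a 3-df interaction test under equal correlation, the noncentrality is λ = (n/2) × Σ(δ_t − mean δ)² / (1 − ρ). If the arm difference rises in equal steps (0, 0.12, 0.24, 0.36), the mean is 0.18 and the sum of squares is 0.0324 + 0.0036 + 0.0036 + 0.0324 = 0.072. Then λ = 45 × 0.072 / 0.3 = 10.8, and power is 0.796 (chi-square) or 0.793 (F). If the difference is spaced by actual months, power is 0.789 or 0.786. The stated 0.80 is reproduced to within 2 points. Inflating 180 for 10% attrition gives 180 / 0.9 = 200, as planned.

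**Both pre-randomization scores as covariates.** In SD² units, the 12-month residual variance with baseline alone is 1 − 0.7² = 0.510. With screening added it is

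1 − (*b*² + 0.7² − 2 × *a* × *b* × 0.7) / (1 − *a*²).

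For *a* = *b* = 0.7: 1 − (0.49 + 0.49 − 0.686) / 0.51 = 1 − 0.576 = 0.424, which is 17% lower.

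| Screening–baseline (*a*) | Screening–follow-up (*b*) | Residual variance | Reduction | Power, 12-month ANCOVA |
|---|---|---|---|---|
| baseline only | – | 0.510 | – | 0.922 |
| 0.7 | 0.7 | 0.424 | 17.0% | 0.960 |
| 0.8 | 0.7 | 0.456 | 10.7% | 0.947 |
| 0.9 | 0.7 | 0.484 | 5.1% | 0.935 |
| 0.95 | 0.7 | 0.497 | 2.5% | 0.928 |
| 0.6 | 0.6 | 0.459 | 9.9% | 0.946 |
| 0.5 | 0.5 | 0.480 | 5.9% | 0.936 |
| 0.7 | 0.6 | 0.486 | 4.7% | 0.934 |
| 0.7 | 0.5 | 0.510 | about 0% | 0.923 |

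In HBI points, the standard error of the 12-month difference is 11.0 × √(variance × 2/90). That is 1.17 with baseline alone and 1.07 in the best row, against a planned difference of 0.36 × 11.0 = 3.96.

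For the joint 3-df test of the arm differences at 3, 6 and 12 months (equal steps, chi-square), power is 0.862 with the baseline covariate alone. With screening added it is 0.933 at 0.7 throughout, and 0.906, 0.883 and 0.872 at *a* = 0.8, 0.9 and 0.95 with *b* = 0.7.

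**Other ways of using the screening score.**
- *Mean of screening and baseline as reference.* The variance of the 12-month change is 1 + (1 + *a*)/2 − (*b* + 0.7). At *a* = *b* = 0.7 this is 0.450, against 0.600 with a single baseline. At *a* = 0.7, *b* = 0.5 it is 0.650, and interaction power falls from 0.786 to 0.761 (F, actual months).
- *Screening as an extra time level (4-df interaction).* Against 0.796 for four points (chi-square, equal steps), power is 0.884 at 0.7 throughout, but 0.772 at *a* = 0.95, *b* = 0.7 and 0.766 at *a* = 0.7, *b* = 0.5.

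Either form can lose power. The covariate form did not raise residual variance in any case tried.

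**The case against.** A reader might infer from the four assessment points that the analysis discards the screening HBI. The article does not support that. The four points are inputs to a power calculation, the analysis text leaves the model's assessments open, and a statistical analysis plan that is not shown may settle the matter. Leaving an available covariate out of a power calculation is merely conservative.

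A reader might also infer that the HBI comparison is underpowered, or that a gain to about 0.88 is there for the taking. Neither follows. The stated 0.80 reproduces. The larger gain extends the 0.7 correlation to a reading that the power section does not cover. If screening and baseline fall close together, a correlation of 0.9 or more is plausible and the gain is a few per cent. Nor is a single baseline costly in itself: used as a covariate it already gives 0.922 at 12 months, so much depends on how baseline is modelled.

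Finally, the Informed consent section describes a brief eligibility screening tool completed by the parent before the consent form is reviewed. The article does not say whether a full scored HBI from that stage is kept as research data for both reporters.

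All of this stands as a limit on the size and certainty of the gain. It does not remove the point about the covariate rule: that rule is written in the article, and it selects baseline variables by between-arm significance.

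**Conclusion.** The point holds as a small efficiency improvement of uncertain size. It is not an error or a contradiction. Two HBI readings per reporter are scheduled before randomization, one is counted in the power assumptions, and the stated covariate routes would admit the second only through chance imbalance or a link with attrition. Over the correlations examined, covariate use lowers the 12-month residual variance by between about 0 and 17%. The upper end needs a correlation of 0.7 throughout. The lower end applies if the two readings are nearly duplicates, or if screening predicts follow-up clearly less well than baseline does.

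This rests on the full HBI being scored and retained at screening. Selection by the three-symptom entry rule may weaken the screening score's correlation with follow-up and so shrink the gain. It does not bias the arm comparison, because the selection precedes randomization.

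**What to change.** Before any unblinded analysis, state that the same reporter's screening HBI and baseline HBI both enter every HBI model as covariates for the 3-, 6- and 12-month scores, for all participants and regardless of imbalance. Do not use the simple mean of the two as reference, and do not add screening as a further time level.

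State the treatment test to match. Once baseline is a covariate, an interaction across the three follow-ups asks only whether the effect changes over time. The test should therefore be of the arm differences at follow-up, jointly or at a named visit.

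Confirm first that the full HBI is scored and kept at screening, and say how a missing screening score is handled. The cost is a few sentences in the analysis plan and one more model term per reporter. No new data, visits or participants are needed, and the sample size stays as it is.
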